## Abstract

**Background:**

Globally, the most important human rights and public health issue that sex workers face is their experience of high levels of violence (Kinnell, 2006, Kinnell, 2008, Alexander, 1999). Deering’s systematic review estimated levels of sexual violence in sex working populations as being between 14% and 54% (Deering et al, 2014).

**Aims:**

This international, robust mixed methods study will explore the frequency of sexual violence against sex workers, barriers in criminal justice and the legal consciousness of sex workers regarding their rights and consent. The hypothesis to be tested is that the safety of sex workers from sexual violence is mediated by the differing legal contexts of sex work environments. We will compare experiences across research sites in the context of legalisation (Nevada USA), client criminalisation (Northern Ireland), decriminalisation (New Zealand) and partial criminalisation (England, Scotland and Wales) [henceforth ESW].

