**Methods:**

An international survey (n = 1,000) will be translated into several languages, to disaggregate experiences by demographic categories (gender, ethnicity, sexual orientation) and sex work sector (including online, street-based and brothels). Interviews (n = 100) with sex workers, police, prosecutors and service providers will be thematically analysed to explore legal consciousness, why the patterns occur and contextualise the statistical findings. These data will be supplemented with comparative legislative, policy and case analysis. Research study data will be used to compare the social factors and legal norms shaping sex workers experiences of sexual violence, justice and support interventions. Recommendations for a ‘best practice’ review of legal improvements and support interventions will be produced following completion of the study.

Given the sensitive nature of the research, robust ethical and data protection mechanisms are in place. The research has ethical approval from each research site, an Advisory Board and trained, paid peer researchers to assist with data gathering, analysis and dissemination. The study will report findings in 2023/2024.

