## 2. Materials and methods

### 2.1 Research aims

The overarching question this study seeks to address is how social, legal, and judicial contexts shape the safety and well-being of people engaging in sex work and, in particular, how context shapes experiences of sexual violence.

Our aims are threefold:

1. Theoretical: to explore sex workers’ experiences and prevalence of sexual violence against the legal norms and boundaries in each of the four legislative models, also examining the least investigated inflictions such as ‘stealthing’ (removal of condom without permission). A desk analysis of legislation and case law in each site, regarding sexual violence and how these laws were operationalised for sex workers. This will assist us to understand how the legal system operates in different jurisdictions and explore how consent, violence and sex work are incorporated in legal judgements. These will be analysed for characteristics, perpetrator, outcome, and tariff.

2. Empirical: to enhance what is known about sex workers’ experiences of the criminal justice system by gathering and analysing new empirical data on how the system operates in different jurisdictions, looking at the impact of legislative models on how sexual violence is responded to, the impact of different settings, and attrition, outcome, and conviction. This will be applied across the four study locations through online surveys of sex workers on sexual violence, which will measure prevalence, experiences, attitudes and understandings of the law, experiences with the police, courts and other agencies, support received and interventions.

3. Practice-based: to facilitate the integration of best practice from a review of what works regarding supporting victims into safety and health-related provision, policies and agencies, led by ‘experts by experience’. These experts are four peer researchers who are sex workers / survivors of sexual violence, who will be trained in research skills, and work as a core part of the research team to interview sex workers who have experienced sexual violence (n = 10 per research site). The research team will also conduct interviews with practitioners (NGOs and statutory health service professionals), police, and criminal justice personnel (n = 10 per research site) to assess issues such as reporting, signposting, available resources, therapy, and criminal justice support.

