#### 2.2.2 Study setting

We will address the research questions above by comparing four different legal environments: legalisation (Nevada USA) where legal brothels are permitted in 10 of Nevada’s 17 counties; client criminalisation (Northern Ireland) whereby following the Nordic model, paying for sexual services is now a summary offence with a maximum penalty of 12 months in prison; decriminalisation (New Zealand) where prostitution, including the operation of brothels is permitted subject to municipal regulation and partial criminalisation (England, Scotland and Wales) whereby the act of selling sex itself is not illegal, but laws have been drafted around a number of facets of sex work such as brothel keeping, soliciting, living of the proceeds of prostitution and so forth.

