#### 2.3.5. Survey sample size

Despite the frequent experiences of violence in some forms of sex work, accessing workers with violent experiences among the entire population of sex workers can be challenging. This population is often under-represented in standard sexual violence surveys, which prevents weighting methodology being employed in this study–this is because there are not sufficient existing independent data with which to compare populations. In other sex work contexts, too many invitations to participate in studies targeted at a few individuals, stigma, and working without legal protection can mean some sex workers are reluctant to engage with research [37].

Unfortunately, the sample for this survey cannot be randomised, as too few responses would be received and there are no intervention arms in this study or reliable population estimates in the sites [38]. However, stratified sample groups for distribution by sector and site have been designed for the recruitment, to attempt to ensure as far as possible that no under- or over-representation of one particular sector of sex work in each research site.

To ensure that we achieve an adequate sample size, calculations were made to test our null hypothesis, namely that there is no difference in the experience of sexual violence by jurisdiction. We used the chi-squared test to test for independence of outcome (binary Yes, No) and jurisdiction (4 levels) with 3 degrees of freedom. Since a significance level of 5% is desired, the chi-squared statistic would need to exceed 7.81. To test the null hypothesis, a minimum sample size of 1760 respondents for the survey would be required, with a minimum of 440 respondents in each jurisdiction.

We derived an alternative hypothesis from a low conservative estimate from Deering et al [39], that circa 15% of sex workers experience violence. We anticipated the overall probability of sexual violence at 15% across all 4 jurisdictions, with 2 jurisdictions differing by 10 points (ie. one records 10% and the other 20%) to be detectable at least 80% of the time. We calculated that we would need a maximum sample size of 3200, where p = 55%. Fifty-five per cent was our upper estimate of sexual violence in sex work [40]. The chi-squared statistic was 7.84 from this calculation.

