#### 2.3.6. Survey data analysis

Survey data analysis will be conducted at mid- and endpoints of the data gathering phase. The mid-point analysis will enable further recruitment where a sample is insufficient and to produce indicative results to inform analysis.

Logistic regression will be used to test the study’s null hypothesis, that there is no significant difference in victimisation by the jurisdiction. In addition, we will assess whether action and harm are mediated by socio-demographic category (gender, ethnicity, age, sexual orientation, citizenship status, income/financial autonomy). Other variables included in the survey are: attitudes to policing, criminal justice response and access to support. Information on conditional consent specific to sex work will also be analysed–for example, under-payment/non-payment, condom removal (‘stealthing’)–as will situations in which consent could not be given; because of intoxication, for example.

Multivariate analysis will be used to identify clusters of respondents by experience of victimisation, jurisdiction and sex work sector with the aim of producing the first statistical international typology of respondent experiences of sexual violence (and justice/support after it) in sex work. Whilst our preference is to use either AHC (Agglomerative Hierarchal Clustering) or PCA (Principal Components Analysis) to generate the clusters, it is unlikely that all variables can be converted into numerical form. Should this not be possible, then our intention is to use Multiple Correspondence Analysis (MCA), which is capable of handling categorical variables. Once our clusters have been generated, we will then explore how they differ in terms of socio-demographic category (gender, ethnicity, age, sexual orientation, citizenship status and income) in different jurisdictions and sex work sectors.

Statistical analysis, reports and publications will be, wherever possible, in line with the SAMPL guidelines [41].

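### With one site per legal model, the comparison of four jurisdictions cannot test the stated hypothesis about legal context, and the limitations do not say so

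*Protocol article*

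**What the plan says.** The hypothesis to be tested, given in the Abstract (Aims) and again in the Introduction, is that "the safety of sex workers from sexual violence is mediated by the differing legal contexts of sex work environments".

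Section 2.2.2 sets out the comparison: "We will address the research questions above by comparing four different legal environments: legalisation (Nevada USA") and then client criminalisation in Northern Ireland, decriminalisation in New Zealand and partial criminalisation in England, Scotland and Wales (ESW). Section 2.1 likewise speaks of experiences "in each of the four legislative models", with the survey run in four study locations.

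The statistical null is worded differently. Section 2.3.5 uses a chi-squared "test for independence of outcome (binary Yes, No) and jurisdiction (4 levels) with 3 degrees of freedom", and "a significance level of 5% is desired". Section 2.3.6 uses logistic regression for the "null hypothesis, that there is no significant difference in victimisation by the jurisdiction". The covariates named there are respondent characteristics: gender, ethnicity, age, sexual orientation, citizenship status and income.

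Section 4.3 lists non-random sampling, self-report, self-selection, under-representation of some groups, no longitudinal follow-up and no inference to other contexts. It does not say that legal model cannot be separated from place.

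**The concern.** The hypothesis is about law, while the test is about place. These coincide only if the four sites differ in nothing relevant except their law. General levels of sexual violence, policing, welfare provision and the make-up of the sex market may all differ between Nevada, Northern Ireland, New Zealand and ESW, and each would move the jurisdiction comparison in the same way as an effect of law.

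The study's own conduct adds further site differences. Section 2.3.2 allows questionnaires to differ by up to 20% between sites. Recruitment runs through site Advisory Boards, platforms and NGOs. Section 4.3 notes that online workers are hard to recruit where such work is illegal, so the legal regime can also affect who is sampled.

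At stake is what the study may conclude. If the null is rejected, the hypothesis as written would appear supported when the test cannot support it. If the null is not rejected, an effect of law could have been offset by other site differences. The Introduction itself warns that violence is used rhetorically in disputes over legal models, so the permitted conclusion should be exact.

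**Working it through.** **1. The plan's own figure.** The 95th percentile of chi-squared with 3 df is 7.815, which agrees with the 7.81 in section 2.3.5. The 3 df are the four jurisdictions minus one.

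**2. Aliasing.** Write the site-level model as logit(p) = intercept + site terms + legal-model terms.
- Intercept and three site indicators: 4 columns, rank 4.
- Add three legal-model indicators: 7 columns. Each model occurs in exactly one site, so each new column repeats a site column and the rank stays at 4.
- Degrees of freedom left to separate model from site: 4 − 4 = 0.

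This does not depend on the number of respondents. Covariates measured on respondents vary within a site and cannot restore the missing rank at site level. With one wave there is no contrast over time within a site either.

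**3. Illustration of size.** The documents give no between-site variance, so the SD below is an assumption. Inputs: prevalence 15% (section 2.3.5); 250 per site (1,000 / 4), 440 per site (the stated minimum) and 800 per site (3,200 / 4); no effect of law; site logits normal with the stated SD; unadjusted 3-df chi-squared test at 5%; 20,000 simulated studies per cell.

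Meaning of the SD: the odds at 15% are 0.15/0.85 = 0.1765. One SD of 0.2 either way multiplies them by 0.819 or 1.221, giving 0.1445 or 0.2155, that is 12.6% or 17.7%. An SD of 0.1 gives 13.8% or 16.3%; an SD of 0.3 gives 11.6% or 19.2%.

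| Between-site SD (logit) | 250 per site | 440 per site | 800 per site |
|---|---|---|---|
| 0 | 4.8% | 5.2% | 5.0% |
| 0.1 | 11.6% | 16.9% | 27.5% |
| 0.2 | 32.8% | 49.0% | 67.2% |
| 0.3 | 56.7% | 73.0% | 85.2% |

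The entries are the proportion of studies that reject. Where the SD exceeds 0 the sites really do differ, so these are correct rejections of the jurisdiction null. The table shows only how often that null would be rejected when law plays no part.

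**4. Comparison with the plan's own alternative.** Section 2.3.5 targets 10% in one jurisdiction and 20% in another. With the other two taken as 15%, the logits are −2.197, −1.735, −1.735 and −1.386, with mean −1.763. The squared deviations sum to 0.188 + 0.001 + 0.001 + 0.142 = 0.332, so the SD is √(0.332/3) = 0.33 (0.29 with divisor 4). The pattern that the survey is sized to detect is therefore about as large as the spread from ordinary site differences with an SD near 0.3.

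**The case against.** Several points on the other side stand.

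- **The nulls already say jurisdiction.** Sections 2.3.5 and 2.3.6 are correctly worded as tests. The fault lies in the hypothesis sentence and in the silence of section 4.3.
- **Legal-regime questions go elsewhere.** Section 2.3 assigns RQs 1, 3, 5, 8, 10 and 13 to the survey, and none of these asks about legal regime. RQ6 goes to the interviews and RQ11 to the desk analysis. The interviews are also meant to put the statistics in context.
- **Law is not claimed to act alone.** The overarching question in section 2.1 names social, legal and judicial contexts together.

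A reader might infer that the plan will report the jurisdiction contrast as a legal effect, citing Aim 2 ("looking at the impact of legislative models on how sexual violence is responded to") and the Abstract ("review of legal improvements and support interventions will be produced following completion of the study"). The documents do not support that. Aim 2 concerns how violence is dealt with, not the victimisation test. The Abstract sentence concerns a best-practice review that is not tied to that test, and no reporting wording is given.

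A reader might also object that no mediator is tested. Section 2.3.6 uses the same verb for socio-demographic categories, apparently meaning only that results vary with them, so this is terminology.

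The one-site-per-model description has some texture. ESW is three nations, but they share one model and enter as one level. Northern Ireland and ESW are both in the UK, which may reduce some differences for that pair, but each still stands alone for its model. Nevada contains legal and illegal work, but no within-Nevada contrast is planned as a test of law, and it would be confounded with sector. None of this gives the stated test a replicated legal model.

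**Conclusion.** The point holds as a mismatch between hypothesis and test. The survey can show whether reported victimisation differs between these four jurisdictions. It cannot show that legal context is the reason, because law and place are completely aliased in the stated test. That conclusion rests only on the documented pairing of models with sites and on the single cross-sectional wave, not on any sample-size figure.

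The rejection rates rest on assumed between-site SDs, 15% prevalence and an unadjusted chi-squared test in place of the planned logistic regression. They should not be read as a false-positive rate of the plan's test. They show that modest site differences would often lead to rejection with no effect of law, and that a larger survey makes this more frequent.

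A within-jurisdiction analysis of attitudes to policing or access to support might seem a way round. It cannot identify a legal effect, because law is largely constant within a site.

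**What to change.** - In the Abstract (Aims) and the Introduction, restate the survey hypothesis as whether reported victimisation differs between these four jurisdictions, in line with the null in sections 2.3.5 and 2.3.6.
- In section 2.3.6, state that a difference between jurisdictions will not by itself be attributed to the legal model.
- In section 4.3, add that legal model is fully confounded with all other differences between sites, including site-specific questionnaire items and recruitment routes, and that respondent-level adjustment does not remove this.
- State that any interpretation about law rests on the interviews (Work Package 2) and the desk analysis (Work Package 3), as supportive and non-causal evidence.

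No change to the design, data collection or statistical test is needed. The cost is the rewording and a more modest headline claim. It is best done before the survey results are analysed.

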**Methods:**

An international survey (n = 1,000) will be translated into several languages, to disaggregate experiences by demographic categories (gender, ethnicity, sexual orientation) and sex work sector (including online, street-based and brothels). Interviews (n = 100) with sex workers, police, prosecutors and service providers will be thematically analysed to explore legal consciousness, why the patterns occur and contextualise the statistical findings. These data will be supplemented with comparative legislative, policy and case analysis. Research study data will be used to compare the social factors and legal norms shaping sex workers experiences of sexual violence, justice and support interventions. Recommendations for a ‘best practice’ review of legal improvements and support interventions will be produced following completion of the study.

Given the sensitive nature of the research, robust ethical and data protection mechanisms are in place. The research has ethical approval from each research site, an Advisory Board and trained, paid peer researchers to assist with data gathering, analysis and dissemination. The study will report findings in 2023/2024.

## 1. Introduction

Globally, the most important human rights and public health issue [1,2] that sex workers face is their experience of violence [3–5], with a systematic review estimating levels of sexual violence as being between 14% and 54% [6]. Whilst there are variances between markets and with more online harms occurring, the marginalisation of sex workers can leave them vulnerable to victimisation and with restricted access to the criminal justice system [7].

Repeat victimisation is common, as is significant under-reporting of crimes to the police [8–11]. Even when cases do get reported, sex workers often experience discrimination [12,13] and mixed responses from police officers [14]. This has led to increased evidence-based calls to make violence against sex workers a public health and human rights priority on national and international policy agendas [15–17].

A detailed examination of the research and policy literature shows the issue of violence against marginalised sex working populations has been dominated by the ‘politics of sex work’, with violence often used rhetorically in battles over what overall legal model would best promote safety [18,19]. A more collaborative public health response is required; to facilitate this, there is an urgent need for studies that document sex workers’ experiences of violence [20]. Crucially, comparative and peer-led research is required, to better document and respond to the contextual factors shaping sexual violence against sex working populations. Greater provision of evidence-based interventions that best promote safety, health and justice for victims are also required in more areas [21–23].

The hypothesis to be tested in this study is that the safety of sex workers from sexual violence is mediated by the differing legal contexts of sex work environments. We will compare experiences across research sites in the context of legalisation (Nevada USA), client criminalisation (Northern Ireland), decriminalisation (New Zealand) and partial criminalisation (ESW).

## 2. Materials and methods

### 2.1 Research aims

The overarching question this study seeks to address is how social, legal, and judicial contexts shape the safety and well-being of people engaging in sex work and, in particular, how context shapes experiences of sexual violence.

Our aims are threefold:

1. Theoretical: to explore sex workers’ experiences and prevalence of sexual violence against the legal norms and boundaries in each of the four legislative models, also examining the least investigated inflictions such as ‘stealthing’ (removal of condom without permission). A desk analysis of legislation and case law in each site, regarding sexual violence and how these laws were operationalised for sex workers. This will assist us to understand how the legal system operates in different jurisdictions and explore how consent, violence and sex work are incorporated in legal judgements. These will be analysed for characteristics, perpetrator, outcome, and tariff.

2. Empirical: to enhance what is known about sex workers’ experiences of the criminal justice system by gathering and analysing new empirical data on how the system operates in different jurisdictions, looking at the impact of legislative models on how sexual violence is responded to, the impact of different settings, and attrition, outcome, and conviction. This will be applied across the four study locations through online surveys of sex workers on sexual violence, which will measure prevalence, experiences, attitudes and understandings of the law, experiences with the police, courts and other agencies, support received and interventions.

3. Practice-based: to facilitate the integration of best practice from a review of what works regarding supporting victims into safety and health-related provision, policies and agencies, led by ‘experts by experience’. These experts are four peer researchers who are sex workers / survivors of sexual violence, who will be trained in research skills, and work as a core part of the research team to interview sex workers who have experienced sexual violence (n = 10 per research site). The research team will also conduct interviews with practitioners (NGOs and statutory health service professionals), police, and criminal justice personnel (n = 10 per research site) to assess issues such as reporting, signposting, available resources, therapy, and criminal justice support.

